## Abstract

**Background:**

Children undergoing anaesthetic induction experience peri-operative anxiety associated with negative outcomes including emergence delirium, short- and long-term maladaptive behaviour and increased postoperative analgesic requirements. This stems from children’s limited ability to communicate, cope, and regulate intense emotions, leading to high dependency on parental emotional regulation. Previous interventions including video modelling, education and distraction techniques before and during anaesthetic induction have demonstrated significant reduction of anxiety levels. No existing interventions combines evidenced-based psychoeducation video with distraction techniques to support parents to moderate peri-operative anxiety. This study aims to test the efficacy of the Take5 video (now referred to as ‘Take5’), a short and cost-efficient intervention for child peri-operative anxiety.

**Methods:**

A randomised, controlled, superiority trial of Take5 compared to standard care. Take5 was developed by paediatric anaesthetists, child psychologists and a consumer panel of parents of children who had experienced surgery and anaesthesia.

Children aged 3–10 years presenting for elective surgery at a quaternary paediatric facility will be randomly allocated to the intervention group or standard care. Intervention group parents will be shown Take5 prior to accompanying their child for anaesthesia induction. Primary outcomes include child and parent anxiety at induction, measured by the Modified Yale Preoperative Anxiety Scale Short Form (mYPAS-SF), the Peri-operative Adult–Child Behavior Interaction Scale (PACBIS) and the Induction Compliance Checklist (ICC). Secondary outcomes include post-operative pain, emergence delirium, parental satisfaction, cost-effectiveness, parent and child psychological well-being at 3 months post procedure and video intervention acceptability.

**Discussion:**

Perioperative anxiety is associated with negative outcome in children including higher pharmacological intervention, delayed procedures, and poor post-recovery outcomes resulting in financial burden on health systems. Current strategies minimising paediatric procedural distress are resource-intensive and have been inconsistent in reducing anxiety and negative postoperative outcomes. The Take5 video is an evidence-driven resource that is designed to prepare and empower parents. The success of Take5 will be evaluated by measuring differences in patient (acute and 3-month), family (satisfaction, acceptability), clinician (feasibility) and health service (cost) outcomes, with each anticipated to benefit children.

**Trial registration:**

Australian and New Zealand Clinical Trial Registry (ACTRN12621001337864) and Children’s Health Queensland Hospital and Health Service Human Research Ethics Committee (HREC/21/QCHQ/73894).

**Supplementary Information:**

The online version contains supplementary material available at 10.1186/s13063-023-07480-0.

## Background and rationale

Research reports 65% to 78% of children experience significant levels of peri-operative anxiety [1–3]. Acute levels of anxiety and distress are associated to psychological issues including mood disorders: depression, anxiety and oppositional defiant disorder and phobias [4], physical impacts such as eating and sleeping disturbances and enuresis [5], and developmental issues notwithstanding cognitive decline and poor development of toileting, independence and maturing of emotional regulation skills [6]. Peri-operative anxiety has also shown to activate physiological responses (cortisol and catecholamines, antibody production and cytokine secretion) that lead to short- and long-term negative outcomes [1]. The most immediate symptoms associated are emergence delirium, expected in 12–18% of all children undergoing anaesthetic induction [7], higher levels of post-operative pain [8, 9], increased analgesic use post-discharge [8] and slower recovery [3, 9]. It has been reported these negative outcomes are experienced by 54% of children within the first 2 weeks, with ongoing negative consequences at 6 (27%) and 12 months (7%) post-surgery [5, 10, 11]. While most children are resilient, approximately 10–13% will experience chronic negative outcomes prolonging physical recovery [4, 12, 13].

At present, pre-operative anxiety is managed through either pharmacological (pre-medication) and/or non-pharmacological intervention. Pharmacological interventions include administering medications that reduce pre-operative anxiety but this can be associated with risk of post-traumatic stress symptoms, increased costs, hospital delays, slower discharge from hospital [3] and, for certain medications, such as benzodiazepine (i.e. midazolam) increased incidence of emergence delirium [14–17]. Alternatively, non-pharmacological interventions such as distraction (i.e. video games/technology), hypnotherapy, clown doctors and acupuncture are preferred due to minimal side-effects, yet evidence of their effectiveness remains variable [18]. While the types of non-pharmacological interventions are increasing, parental presence remains the most employed and studied despite mixed findings surrounding its effectiveness.

A Cochrane review which examined 28 trials, totalling 2681 children over two decades concluded parental presence had no effect on child’s levels of anxiety, distress, or improved child cooperation during anaesthetic induction [18]. However, an evidenced-based review by Chundamala [19] found mixed results, providing further insight. Specifically, a retrospective cohort analysis by Kain of 568 participants across 7 years, of children aged 2–12, found ‘calm parents’ significantly reduced anxiety among ‘anxious children’ and ‘anxious parents’ significantly increased anxiety among ‘calm children’ [20]. However, no effects were found between ‘calm parents’ to ‘calm children’ or ‘anxious parents’ to ‘anxious children’ [20]. Similarly, a randomised control trial (RCT) by Johnston [21] among 134 children aged 2–8, found that ‘anxious parents’ increased anxiety for children, whereas the presence of ‘calm parents’ made no difference whether they were present or absent during an anaesthetic induction on the child’s level of anxiety. These two studies imply it is not parental presence alone but parental emotional state that significantly influences child anxiety, particularly when there is a misalignment between child and parent emotional states. Furthermore, ceiling and floor effects were reported, such that once a certain level of anxiety or calmness was reached, parental presence with an aligned emotional state did not change the child’s emotional state. This indicates value in interventions that address parental anxiety.

Of most interest is Patel’s study of 112 children aged between 4 and 12, which found the greatest decrease in paediatric anxiety through parental presence was in conjunction with distraction, specifically when patients were provided a hand-held device (i.e. video game) by the research team [22]. The study found this combination more effective compared to parental presence alone or parental presence with the administration of midazolam [22]. That is, the inclusion of a video game provided an opportunity for parents to engage in coping-promoting behaviour towards their child. Supporting the use of distraction are two systematic reviews that found game-based interventions (i.e. gamification or virtual reality) during paediatric anaesthetic induction were effective in reducing anxiety for the child and parent [23, 24]. This finding suggests that parent emotional states can be influenced and is further enhanced with distraction, an important consideration to maximising the impact of parental presence.

A key reason why parental presence is heavily relied upon despite a lack of evidence on its effectiveness is the significant association between the parent’s and the child’s emotional regulation. Specifically, children are dependent on their parents to moderate their emotions, and theory-driven research supports that parental procedural behaviour mediates parental psychological distress and child procedural distress [1, 25]. An important barrier, however, to the impact of parental presence on peri-operative anxiety is parental anxiety. Specifically, parents can also experience ongoing distress from a child’s medical procedure and associated illness/injury [11]. Approximately 25% of parents report heightened anxiety and traumatic stress symptomology in the first month, and 5% have ongoing symptoms at 6 months [25]. Consequently due to the parent’s own anxiety, their ability to support their child’s emotional regulation is diminished [21]. That parents also experience distress provides a potential explanation for the conclusion of the Cochrane review that parental presence alone was ineffective in reducing child’s anxiety [18]. This relationship between parent and child emotions is the theoretical foundation of the current study. As parents prefer to be present during anaesthetic induction [26], this study targets two key levers intervening the parent’s emotional state and equipping parents with coping-promoting behaviours including distraction strategies, with the overall goal of reducing child anxiety.

Presently, two seminal studies aimed at intervening negative parental presence using video preparation and modelling, have found evidence for a concomitant and significant reduction in peri-operative anxiety among children. One study evaluated the ADVANCE program, a multicomponent behavioural program targeting anxiety reduction through distraction, video modelling, education and coaching parents regarding positive and negative coping behaviours [14]. Overall, the program was effective at significantly reducing peri-operative anxiety among children during anaesthetic induction compared to pre-medication, parental presence and standard hospital care groups [14]. These children also had significantly lower incidences of emergence delirium, required less analgesia and demonstrated faster recovery times [14]. A major limitation of the ADVANCE program, however, is the limited feasibility and application to many hospital settings, as it required extensive lead up time and intensive parental coaching [27].

The second study by Bailey and colleagues, tested a brief video intervention on 93 parents of children aged 2–10 years, supplied on the day of the surgery [27]. The video provided information about the procedure, addressed parental anxiety and explained the benefits of distraction strategies. Parents in the intervention group tended to report higher self-efficacy regarding their role during the induction [27]. This is important as parents have identified that it was important for them to be present to support their child’s procedures and this increase in self-efficacy would like increase their confidence and lower their levels of anxiety [26, 27]. Nevertheless, no statistical differences were found between groups on child peri-operative anxiety behaviour, emergence delirium, postoperative pain, post operative analgesia, or recovery time. A significant limitation of this study was that it did not measure parental behaviour to determine whether the intervention was successful in changing parental behaviour, the key mediator of child procedural anxiety [28].

It is important to assess accessibility, mode, and timing of delivery to understand contributing factors to effectively administer a video intervention. Presently, evidence-based video interventions like ADVANCE [14] by Kain and colleagues for perioperative anxiety are resource intensive and time-consuming and is unlikely to be feasible in most health care settings [27]. Conversely, brief video interventions, particularly those that address parental anxiety, are a promising non-pharmacological intervention but are currently under-evaluated. Lastly, there is a lack of understanding of how parents consolidate information under a stressful environment (i.e. peri-operative) and limited identification of the potential enablers and barriers to parents maintaining a calm state.

Based on theory-driven research [28, 29], Brown and colleagues developed and feasibility tested the Take5 video intervention, designed for parents of children undergoing burn wound care. Initial results indicated lower rates of distress and pain for children of parents who had received the video, compared to an observational cohort (unpublished). This intervention was the foundation for the current Take5 intervention for parents of children undergoing anaesthetic induction. A group of professionals, in consultation with a parent consumer group, forward-developed Take5 for anaesthetics to address the current gaps in the literature. Specifically, a representative parent consumer group informed the appropriateness of language, tone, and sensitivity required in communicating to parents in anxious states based on lived experiences. Furthermore, the Take5 intervention was tested for acceptability with 10 families attending elective surgery prior to data collection for further refinement of the intervention. The end product was a 5-min animated video that aimed to provide parents with procedural preparation, behavioural coaching to engage the child in distraction, and psychological self-coping strategies based on the evidence-based Acceptance Commitment Therapy Framework [30].

The intervention will be tested against a control group which will receive standard of care consisting of preoperative preparation provided by the anaesthetic doctors including a description of the anaesthesia management and a discussion of the risks involved.

### Objectives

The study aims to test the efficacy of the Take5 video intervention at reducing child and parent anxiety with the following key objectives:Demonstrate the efficacy of the ‘Take5’ resource in reducing preoperative anxiety and postoperative adverse outcomes via a RCT at a quaternary paediatric facility.Demonstrate the efficacy of ‘Take5’ in reducing adverse psychological and health-related quality of life 3 months post-surgery, as well as improving parental satisfaction of care.Demonstrate the health economic benefits of the ‘Take5’ resource.

### Hypotheses

Based on its prior initial success, it is expected that a ‘Take5’ video tailored to the peri-operative context will demonstrate significant reductions in peri-operative child anxiety and improve post-operative outcomes. Specifically, it is hypothesised:Children in the Take5 intervention group will demonstrate less peri-operative distress behaviours than children in the control group.Children in the Take5 intervention group will report less peri-operative anxiety than children in the control group.Parents in the Take5 intervention group will report less peri-operative anxiety than parents in the control group.

Secondary hypotheses are:Children of parents in the intervention condition will experience lower rates of post-operative pain scores and emergence delirium scores, and faster time to discharge compared to children in the control group.Children in the Take5 intervention will have improved health-related quality of life scores and reduced behavioural difficulties including symptoms of anxiety and depression at 3 months after the surgery compared to children in the control group.Parents in the Take5 intervention will report less general anxiety and depressive symptoms at 3 months after their child’s surgery compared to parents in the control group.

### Trial design

This single-centre, randomised controlled efficacy trial with two parallel arms is comparing the clinical effectiveness and cost-effectiveness of two approaches to reducing peri-operative anxiety in children:Standard care: preoperative preparation provided by the anaesthetic team including a description of the anaesthesia management and a discussion of the risks involved.Take5: a brief video provided to parents prior to their child undergoing anaesthetic induction.

The RCT is reported in accordance with the Standard Protocol Items: Recommendations for Intervention Trials (SPIRIT) 2013 statement for clinical trial protocols [31].

## Methods: participants, interventions, and outcomes

### Study setting

This trial began recruitment on 22 June 2022 and is expected to continue recruitment until March 2023. The study is based at a quaternary paediatric facility in Queensland, Australia. The facility admits approximately 6500 children (neonates to 17 years old) annually for elective procedures [32].

### Eligibility criteria

Eligible participants are patients aged between 3 and 10 (inclusive) years old undergoing elective day-case procedures at a quaternary paediatric facility who do not meet the following exclusion criteria. Exclusion criteria consist of children (1) with a diagnosed pervasive developmental disorder or global developmental delay documented in their medical records, (2) requiring emergency surgery, (3) under the care of the Department of Child Safety, (4) who have a parent with insufficient English to provide consent without the aid of a translator, (5) deemed by anaesthetist as requiring pre-medication (i.e. midazolam) prior to a general anaesthetic, and (6) deemed highly anxious by the anaesthetist who will not benefit from additional personnel.

### Interventions

Take5 was designed to be implemented as a universal tool for all parents who attend their child’s medical procedure, to increase parental psychological coping and associated behaviours, to target the child’s procedural coping. Given the acute delivery design, Take5 was intentionally brief to be provided via a tablet in a clinical environment on the day of surgery prior to the procedure.

Specifically, Take5 communicated three key messages: What to expect during the patient journey (procedural preparation), the benefits of distraction to the child (reinforcing parental behaviour), and psychoeducation to provide general coping strategies for the parent to manage personal distress during and after the child’s procedure. Procedural preparation was communicated because patients and parents commonly express unmet expectations for information [33]. Positive behavioural reinforcement was used because fear-based messaging is thought to have unintentional consequences [34]. The psychoeducation was modelled on Acceptance Commitment Therapy to assist with normalising feelings of distress for parents [22]. An acceptability and feasibility study (unpublished) of 10 parents receiving Take5 demonstrated good acceptability, and increased positive parenting behaviours, and reduced child procedural distress, compared to data from Brown et al.’s observational study [28].

The ‘Take5’ video was adapted by the authors (a group of psychologists and anaesthesiologists) for anaesthetic induction. The authors initially consulted the hospital’s consumer panel of parents to understand what preparatory information parents valued regarding the anaesthetic induction, what helped their child have a positive medical experience, and what advice they had for parents to cope while supporting their child. The panel feedback was documented, thematically summarised, and agreed by the authors as in or out of scope for the video. In-scope feedback pertained to the key messages and generalisability to other hospital locations. Using the in-scope panel feedback, the authors adapted the procedural preparation, parental behaviour and psychoeducation components of Take5 to ensure appropriate for anaesthetic induction. The authors presented a drafted video script back to the consumer panel for validation and further feedback. The panel provided positive comments on the script and suggestions for the animation.

The video was developed using a VideoScribe web subscription, and images were chosen to minimise gender, ethnicity, and language biases. Further parental feedback was elicited through 10 data collection ‘dry runs’, with small changes made to the video prior to commencing recruitment.

### Outcomes

The primary outcome of the study is child peri-operative anxiety as measured by the modified Yale Preoperative Anxiety Scale Short Form (mYPAS-SF) [35], the Peri-operative Adult–Child Behavior Interaction Scale (PACBIS) [36], the Visual Analogue Scale for Anxiety (VAS-A) [37], and the Induction Compliance Checklist (ICC) [38].

The secondary outcomes include:Child post-operative pain measured during recovery via observation using the Face, Legs, Activity, Cry and Consolability Pain Scale (FLACC) [39];Child emergence delirium scored during recovery using the Cornell Assessment for Paediatric Delirium (CAP-D) [40];Parent satisfaction with procedure via a purpose-built survey of feedback via a numeric rating scale (1–10 of increasing satisfaction);Parent and child 3-month psychosocial outcomes: measured using validated measures of adult psychological well-being, specifically the Depression, Anxiety and Stress Scale (DASS-21) [41], child physical, mental and social health the Patient-Reported Outcomes Measurement Information System (PROMIS [42] and PROMIS Early Childhood [43]) and health-related quality of life using the Child Health Utility instrument (CHU9D) [44];Acceptability: A semi-structured interview developed in specifically for the ‘Take5’ video will assess acceptability of delivery and content of ‘Take5’; andCost-effectiveness via the cost of intervention, and direct and indirect healthcare costs to the healthcare system.

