### Sample size

The primary outcome of this study is children’s anxiety at anaesthesia induction as measured by the mYPAS-SF. Our estimate of effect is based on the validation study of ‘Take5’ in a cohort of children with burn-injuries (unpublished) and the ADVANCE preparation program [14]. Assuming a clinically meaningful difference in anxiety (15-point difference on the mYPAS-SF) [8, 14], with a mean control group score = 55 and a mean intervention group score = 40, a corresponding effect size of 0.61 was used for these analyses. Therefore, a sample of 50 participants per group is anticipated to provide > 90% power to detect this effect size (α < 0.05).

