### Statistical methods

#### Statistical methods for primary and secondary outcomes

Interrater reliability will be conducted by having two researchers independently scoring every anaesthetic induction for observational measures including mYPAS-SF, PACBIS and ICC. Following training in the measures, reliability will be attained by the researchers independently scoring sets of five videos, and statistically comparing results using intra-class correlations, as recommended for ordinal data [46]. The researchers will discuss any discrepancies in scoring, before independently scoring another set of five videos, until reliability is achieved. To test for inter-rater drift, reliability was assessed at 20% intervals throughout data collection.

Between group comparisons of primary and secondary outcomes will be compared using general linear modelling, to account for relevant control variables. Secondary outcomes that are non-continuous will be analysed using Pearson’s chi-squared analysis. The primary analysis will be ‘intention-to-treat’. A within-trial cost-effectiveness analysis will be conducted. Resource consumptions (and cost) will be collected for both arms (standard and interventions). Primary outcomes of behaviour and anxiety, and the secondary outcome (quality of life) will be used. Incremental cost and effectiveness (outcomes) will be calculated, and the incremental cost per effectiveness ratio (ICER) will be the primary result. Data will be reported in accordance with the Consolidated Standards of Reporting Trials (CONSORT) 2010 statement [47].

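### The primary outcome is defined in three incompatible ways, and only one of them, mYPAS-SF at induction, is powered

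*Protocol article*

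**What the plan says.** Three places in the protocol article define the primary outcome.

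- **Sample size:** "The primary outcome of this study is children’s anxiety at anaesthesia induction as measured by the mYPAS-SF". One instrument, child only, at induction. The 15-point difference, the effect size of 0.61, the 50 per group and the single alpha of 0.05 all belong to this definition.
- **Outcomes:** "The primary outcome of the study is child peri-operative anxiety as measured by the modified Yale Preoperative Anxiety Scale Short Form (mYPAS-SF"), followed by PACBIS and then "the Visual Analogue Scale for Anxiety (VAS-A) [37], and the Induction Compliance Checklist (ICC) [38"]. Four instruments, child only, no time point.
- **Abstract, Methods:** "Primary outcomes include child and parent anxiety at induction", measured by mYPAS-SF, PACBIS and ICC. Three instruments without VAS-A, and parents as well as children.

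Two further places bear on it. Among the three hypotheses listed before the secondary ones is this: "Parents in the Take5 intervention group will report less peri-operative anxiety than parents in the control group". In the statistical methods, the cost-effectiveness text uses the plural: "Primary outcomes of behaviour and anxiety, and the secondary outcome (quality of life) will be used". The analysis rule there is the same for every outcome: "Between group comparisons of primary and secondary outcomes will be compared using general linear modelling, to account for relevant control variables".

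Participant timeline and Table 1 have mYPAS-SF, PACBIS and VAS-A recorded at both t1 (holding bay) and t2 (induction).

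**The concern.** A primary outcome fixes in advance which comparison decides whether the trial succeeded. Here the answer depends on the section read. The definitions differ in the number of instruments, in whose anxiety counts, and in whether the time point is fixed.

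The instruments are not interchangeable. By the article's own description of t2, PACBIS records parent and child behaviour and ICC records the child's cooperation, while mYPAS-SF records the child's anxiety. They could disagree. A benefit on ICC with nothing on mYPAS-SF would be a primary success under the Outcomes section and the abstract, and a failure under Sample size. At stake are the false-positive rate of the primary claim and the freedom to choose among definitions once results are known.

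**Working it through.** **1. The definitions side by side**

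| Section | Instruments | Whose anxiety | Time |
|---|---|---|---|
| Sample size | 1: mYPAS-SF | child | induction |
| Outcomes | 4: mYPAS-SF, PACBIS, VAS-A, ICC | child | not given |
| Abstract | 3: mYPAS-SF, PACBIS, ICC | child and parent | induction |

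No reading satisfies all three rows. VAS-A is primary in one row only, parent anxiety in one row only, and PACBIS and ICC in two of three.

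**2. The plan's own power figure**

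Inputs from Sample size: means 55 and 40, effect size d = 0.61, n = 50 per group, alpha 0.05, sidedness not stated. The implied SD is 15 / 0.61 = 24.6. The standardised mean difference is d × √(n/2) = 0.61 × √25 = 3.05.

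- One-sided: Φ(3.05 − 1.645) = Φ(1.405) = 92.0% (noncentral t: 91.7%).
- Two-sided: Φ(3.05 − 1.960) = Φ(1.090) = 86.2% (noncentral t: 85.5%).

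The stated power above 90% is therefore reproduced by a one-sided test only. Two-sided 90% would need 2 × ((1.960 + 1.282) / 0.61)² = 56.5, so 57 per group (58 by t-test).

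**3. False-positive rate if any listed instrument may claim success**

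Assumptions: no true effect on any instrument, each tested at two-sided 5%, one score per instrument. For k independent tests the rate is 1 − 0.95^k. For correlated tests it is the probability that the largest of k equally correlated standard normal statistics exceeds 1.96 in absolute value. The article gives no correlations, so a range is shown.

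| Correlation (assumed) | 3 instruments | 4 instruments |
|---|---|---|
| 0 | 1 − 0.95³ = 14.3% | 1 − 0.95⁴ = 18.5% |
| 0.5 | 12.5% | 15.6% |
| 0.9 | about 8% | about 9% |

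**4. Price of keeping several primaries instead**

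Bonferroni, two-sided, with d = 0.61 assumed for each instrument and n = 50, against the 86.2% baseline:

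- Three instruments: alpha 0.05 / 3 = 0.0167, power Φ(3.05 − 2.394) = 74.4%; 73 per group for 90%.
- Four instruments: alpha 0.05 / 4 = 0.0125, power Φ(3.05 − 2.498) = 71.0% (noncentral t: 69.3%); 77 per group for 90%.

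A single primary carries no such cost.

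**The case against.** The best defence is that Sample size settles the matter: it names one outcome, one instrument and one time, it is the only powered version, and a reader can hold the report to it. That weakens any claim that the result would be uninterpretable, and it points to the right repair. It does not remove the conflict. The Outcomes section, where a reader looks for the definition, opens in almost the same terms and gives a different answer, and the abstract gives a third.

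It is also fair to say that an analysis plan or full protocol, not shown here, may contain a multiplicity rule. That stands. A reader might infer that the trial has no multiplicity control and tests each instrument at 5%; the article says neither. It states one alpha, attached to mYPAS-SF. The error rates above are therefore conditional. But condensing a protocol does not explain three different definitions, and an unseen plan cannot make the published ones agree.

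A reader might also count every instrument, rater and time point, reach ten contrasts, and quote 1 − 0.95^10 = 40%. No section asserts that set. The Outcomes section is confined to the child, which excludes the parents' own VAS-A ratings. The abstract and Sample size are confined to induction, which excludes t1. Ten is a union across sections and should not be used.

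Independence is implausible, since all scores come from one parent-child pair within a short period. The correlated rows matter more, and at 0.9 the excess over 5% is modest.

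Two of the supporting places are weaker than the rest. The first three hypotheses are not labelled primary; that follows only from the secondary list coming after them. The plural in the statistical methods concerns inputs to the cost-effectiveness analysis. Finally, parents rate VAS-A knowing their allocation, but that is a separate question of bias.

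**Conclusion.** The point holds as a contradiction within the article: three definitions of the primary outcome that cannot all be true, with no statement of which governs. Its consequence for error depends on use. If any one of three or four instruments could carry the primary claim at two-sided 5%, the false-positive rate would lie between about 8% and 18.5%, depending on the number of instruments and an unknown correlation. Every case exceeds 5%. If mYPAS-SF at induction is the sole primary, no inflation of the primary test arises. The article does not show that multiplicity is uncontrolled, and it does not support a count of ten primary contrasts.

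**What to change.** Name one primary outcome throughout: mYPAS-SF at t2 (induction), from the blinded video score, tested at 5%. This matches the existing powering. It also uses the filmed assessment, whose coder is masked, whereas the research assistant cannot be. Make PACBIS, ICC, both the parent's own and the parent-rated child VAS-A, and all t1 scores secondary. Align the abstract, Hypotheses, Outcomes and Statistical methods (including the economic text) with Sample size before any unblinded analysis. No alpha adjustment of the primary test is then needed.

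State the sidedness in the same change. If the test is two-sided, replace the claim of more than 90% power with about 86%.

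The cost is that the other instruments lose primary status. Recruitment began in June 2022, so this is a change of outcomes during the trial, and the Harms section sets out who must be told: investigators, ethics committees, the registry and the publishing journal, with the participant information and consent documents updated. That is more than a wording correction, but it needs no extra participants or data collection.
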